### Outcomes

#### Primary outcome measures

Our primary outcome is vaccine hesitancy (including COVID-19 vaccine hesitancy). We will ask participants how much they agree or disagree with statements related to perceived vaccine safety as well as their attitudes, preferences, beliefs, and hesitancies regarding regular vaccines and the COVID-19 vaccine, respectively [16]. In the statistical analysis process, we will use nine questions to measure the degree of vaccine hesitancy in general and seven questions to measure the COVID-19 vaccine hesitancy specifically. Then we will normalize the final score to a range of 1–5 for both measures for comparison, which higher scores indicate higher degrees of vaccine hesitancy. These questions are shown in Table 1 and the data elicited from this survey will enable us to achieve objective 1.

**Table 1 Tab1:** The (COVID-19) vaccine hesitancy items

Vaccine hesitancy	COVID-19 vaccine hesitancy
L1. Vaccines are important for my health	L1. COVID-19 vaccines are important for my health
L2. Vaccines are effective	L2. COVID-19 vaccines are effective
L3. Having myself vaccinated is important for the health of others in my community	L3. Having myself vaccinated with a COVID­19 vaccine is important for the health of others in my community
L4. All vaccines offered by the government programme in my community are beneficial.	L4. All COVID-19 vaccines offered by the government program in my community are beneficial
L5. New vaccines carry more risks than older vaccines	L5. COVID-19 vaccines from other countries carry more risks than vaccines from my country
L6. I trust the information I receive about shots	L6. The information I receive about COVID-19 vaccines from the vaccine program is reliable and trustworthy
L7. Getting vaccines is a good way to protect myself from disease	L7. Getting COVID-19 vaccines is a good way to protect myself from COVID-19
L8. I am able to openly discuss my concerns about shots with my doctor	L8. Generally, I do what my doctor or health care provider recommends about COVID-19 vaccines for myself
L9. I am concerned about serious adverse effects of vaccines	L9. I am concerned about serious adverse effects of COVID-19 vaccines
L10. People do not need vaccines for diseases that are not common anymore	L10. I do not need COVID-19 vaccines if it’s not a pandemic anymore
L11. I believe that many of the illnesses shots prevent are severe	L11. I am concerned that COVID-19 vaccines might not prevent the disease
L12. It is better to get fewer vaccines at the same time	L12. I am concerned that COVID-19 vaccines might not be safe
L13. People get more shots than are good for them	
L14. It is better to develop immunity by getting sick than to get a shot	

*Note: the survey tool was designed based on [16], which requires the level of agreement from “strongly disagree” to “strongly agree”

#### Secondary outcome measures

Our secondary outcomes include participants’ behavioral intent to get vaccinated as well as participants’ level of hope. In order to reduce the social desirability bias often associated with direct questioning about sensitive items [15], we will use the unmatched count or list randomization approach to devise a series of list experiments [17]. Four list experiments will be used, as shown in Table 2. For each experiment, the control group will receive a list of three items. Participants are asked how many items they are likely to do in the coming months without stating which ones they chose. The treatment group will get the identical item lists but with one additional “sensitive” item relating to their behavioral intent to get vaccinated or encourage their loved ones to do so. For example, imagining that the control group select 1 out of the 3 items on average while the treatment group select 1.3 out of the 4 items, with the assumption that the average acceptance of these two cohorts is the same, we can conclude that the prevalence of participants who would get vaccinated against COVID-19, is 20%. We have designed the list of experiments in accordance with published best practices [17], and these data will be used to assess objective 2.

**Table 2 Tab2:** List experiments in the trial

**List 1: COVID vaccine—self uptake**	
1. Brush my teeth at least twice daily	
2. Begin learning a new language	
3. Smoke cigarettes or vape	
4. Get vaccinated against COVID-19 when the vaccine is available for me^*^	
**List 2: COVID vaccine—recommendation**	
1. Recommend a show or movie to my friend	
2. Encourage a friend to seek routine dental care	
3. Allow a friend to drive home even though I think they may have had too much to drink	
4. Encourage a friend or family member to get vaccinated against COVID-19 when the vaccine is available for them^*^	
**List 3: routine vaccine—self uptake**	
1. Wash my hands before eating	
2. Take up a new sport	
3. Have unprotected sex with someone who is not my long-term partner	
4. Get a routine vaccine (for example, flu vaccine, tetanus booster shots, hepatitis B vaccine) if the doctor recommends it^*^	
**List 4: routine vaccine—recommendation**	
1. Try to get my family to eat more fruits and vegetables	
2. Perform a routine check of the batteries in our smoke detectors	
3. Encourage a friend to get a tattoo or body piercing	
4. Encourage a friend or family member to get a routine vaccine (for example, flu vaccine, tetanus booster shots, hepatitis B vaccine) if the doctor recommends it^*^	

Note: In each trial arm, both groups will receive four lists. For each list, the control group will get the first three items only; the treatment group will receive the three items and the fourth sensitive item, indicated by an asterisk (*). Each list experiment will be preceded by the question: “In the coming 3 months, how many of the following things are you likely to do? I do not need to know which of these things you are likely to do, just how many.”

Second, we will assess participants’ level of hope using the Adult Hope Scale [18], a 12-item scale measuring participants’ level of hope (Table 3). The Adult Hope Scale is comprised of two subscales relating to Snyder’s cognitive model of hope: (1) Agency (goal-directed energy) and (2) Pathways (planning to accomplish goals) [11]. The 12 items include 4 Agency items, 4 Pathways items, and 4 distractors. Participants are asked to respond using an 8-point Likert-type scale ranging from Definitely False to Definitely True. As recommended in the literature, we will refer to the scale as “The Future Scale” within the survey experiment.

**Table 3 Tab3:** The future scale

Items	Response
I1. I can think of many ways to get out of a jam.	1. = Definitely false
I2. I energetically pursue my goals.	2. = Mostly false
I3. I feel tired most of the time.	3. = Somewhat false
I4. There are lots of ways around any problem.	4. = Slightly false
I5. I am easily downed in an argument.	5. = Slightly true
I6. I can think of many ways to get the things in life that are important to me.	6. = Somewhat true
I7. I worry about my health.	7. = Mostly true
I8. Even when others get discouraged, I know I can find a way to solve the problem.	8. = Definitely true
I9. My past experiences have prepared me well for my future.	
I10. I’ve been pretty successful in life.	
I11. I usually find myself worrying about something.	
I12. I meet the goals that I set for myself.	

Note: Items 2, 9, 10, and 12 make up the agency subscale. Items 1, 4, 6, and 8 make up the pathway subscale. Researchers can either examine results at the subscale level or combine the two subscales to create a total hope score

We also aim to measure the difference of the outcomes above between the three *intervention arms a* (storytelling-instructional-humor), *b* (storytelling-analogy), and *c* (storytelling emotion-focused). These data will be used to assess objective 3.

### Sample size

To calculate the sample size needed for pairwise comparison between three groups, we used a one-way analysis of variance (ANOVA). The formula is as follows.
$$ {n}_A=\left({\sigma}_A^2+\frac{\sigma_B^2}{\kappa}\right){\left(\frac{Z_{1-\frac{\alpha }{\tau }}+{Z}_{1-\beta }}{\mu_A-{\mu}_B}\right)}^2 $$

where *κ*, the matching ratio, is equal to 1 in our study; *μ*_*A*_ and *μ*_*B*_ are the means of group A and group B; *σ*_*A*_ and *σ*_*B*_ are the standard deviations; *α* = 0.05 and *β* = 0.2 are the type-I and type-II error, respectively; Z is the quantile function; and *τ* = 2 is the number of comparisons to be made. For vaccine hesitancy (and COVID-19 vaccine hesitancy), we assume that the means of two arms are 2.00 and 2.01, which represents the level of vaccine acceptance of this arm (1 means total acceptance and 5 means complete refusal), the standard deviations are the same, 0.10. To detect a difference of 0.01 between the vaccine hesitancy between arms, we can calculate the total minimal sample size is *n*_*A*_ = *n*_*B*_ = *n*_*C*_ = *n*_*D*_ = 1570, so the *N* = 6280. To test the sensitivity of the result, we can change our assumption and increase the standard deviation to 0.12, i.e., *σ*_*A*_ = *σ*_*B*_ = 0.12. Then we have *n*_*A*_ = *n*_*B*_ = *n*_*C*_ = *n*_*D*_ = 2260 and *N* = 9040. To achieve a higher level of accuracy, we will recruit 12,000 participants in each country for this study.

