### Trial design

Our study is a multi-site, parallel group, randomized controlled trial (RCT) comparing the effectiveness of each of the short intervention videos with each other and with no video (the control condition). Via the online research platforms, participants will be randomly assigned to four intervention arms (Video A: storytelling-instructional-humor approach, Video B: storytelling-analogy approach, Video C: storytelling-emotion-driven approach) and a control arm (no video). Participants will be randomized at a 1:1:1:1 ratio (Fig. 1). In each trial arm, there is a questionnaire survey, arranged in the following order. *Intervention arm a*: participants will receive the storytelling-instructional-humor video, followed by the survey. *Intervention arm b*: participants will receive the storytelling-analogy video, followed by the survey. *Intervention arm c*: participants will receive the storytelling-emotion-focused video, followed by the survey. *Control arm*: participants will first receive the survey. After survey responses are submitted, participants in the control arm will be given access to the video interventions arranged in a single loop (to ensure post-trial access to treatment).

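### The sample-size formula's comparison count of 2 only supplies the two-sided 5% value, so the stated minima per arm allow for no multiple comparisons and match no comparison set in the protocol

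*Protocol article*

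**What the plan says.** All references are to the protocol article.

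- **Sample size** opens with "To calculate the sample size needed for pairwise comparison between three groups". Its formula takes the normal quantile at 1 - alpha/tau, where tau = "2 is the number of comparisons to be made". Alpha is 0.05, and beta = "0.2 are the type-I and type-II error, respectively".
- For the effect, "we assume that the means of two arms are 2.00 and 2.01", and "the standard deviations are the same, 0.10". This gives 1,570 per arm and N = 6,280 over four arms. A sensitivity case, to "increase the standard deviation to 0.12", gives 2,260 per arm and N = 9,040. The section then sets recruitment at 12,000 per country.
- **Trial design** describes four arms: "Participants will be randomized at a 1:1:1:1 ratio". The purpose is "comparing the effectiveness of each of the short intervention videos with each other and with no video".
- **Explanation for the choice of comparators** says that the video-control comparisons quantify each video's effect, and describes the video-video comparisons as exploring differences between approaches.
- **Methods for additional analyses** plans both country-specific and pooled analyses.

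**The concern.** One symbol is doing two jobs. It is labelled as a count of comparisons, so a reader will take the minima as already adjusted for multiplicity. Numerically it is only the 2 that turns a one-sided 5% level into a two-sided one. The label also fits nothing else in the protocol: four arms yield three contrasts with control and three between videos, and the same paragraph speaks of three groups while listing four arm sizes and multiplying by four.

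At stake is the protocol's justification of its size. If the comparison count is meant as defined, the printed minima are too low, and the planned 3,000 per arm per country stands closer to the requirement than the comparison with 2,260 suggests.

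**Working it through.** **Inputs.** From Sample size: difference 0.01, SD 0.10 or 0.12, alpha 0.05, power 80%, ratio 1. From Trial design: four equal arms, so 12,000 / 4 = 3,000 per arm per country and 24,000 / 4 = 6,000 per arm pooled. Sidedness is not stated.

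**Formula.** n per arm = 2 (SD/0.01)² (z_crit + 0.8416)². The factor 2 (SD/0.01)² is 200 at SD 0.10 and 288 at SD 0.12.

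**1. Reproduce the stated figures.** With tau = 2, z_crit = z(0.975) = 1.960, and (1.960 + 0.8416)² = 7.849.
- SD 0.10: 200 × 7.849 = 1,569.8, so 1,570 per arm and N = 6,280. This matches.
- SD 0.12: 288 × 7.849 = 2,260.5, against 2,260 stated. This matches apart from rounding.

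A one-sided 5% test of one comparison would give 1,237 and 1,781, which do not match. The stated minima are thus those of a single unadjusted two-sided 5% comparison.

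**2. Use tau as it is defined, for the three video-control contrasts.**

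| Reading | z_crit | n per arm, SD 0.10 | n per arm, SD 0.12 |
|---|---|---|---|
| Printed formula, tau = 3: z(1 - 0.05/3) | 2.128 | 1,764 | 2,540 |
| Two-sided Bonferroni: z(1 - 0.05/(2×3)) | 2.394 | 2,094 (N = 8,376) | 3,016 (N = 12,064) |

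For example, 288 × (2.394 + 0.8416)² = 3,015.1, rounded up to 3,016. Both readings exceed the stated minima.

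**3. Power at the stated minima.** Power = Φ(0.01 / (SD √(2/n)) - z_crit). At SD 0.10 and n = 1,570, the first term is 0.1 × √785 = 2.802.
- Unadjusted: Φ(2.802 - 1.960) = 80.0%.
- Printed formula, tau = 3: Φ(2.802 - 2.128) = 75.0%.
- Two-sided Bonferroni, three contrasts: Φ(2.802 - 2.394) = 65.8%.

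The figures at SD 0.12 and n = 2,260 are practically the same.

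**4. Power at the planned size, three contrasts, two-sided Bonferroni.**
- 3,000 per arm, SD 0.10: Φ(3.873 - 2.394) = 93.0%.
- 3,000 per arm, SD 0.12: Φ(3.227 - 2.394) = 79.8%.
- 6,000 per arm pooled: 99.9% at SD 0.10 and 98.5% at SD 0.12, taking the same difference and SD in both countries.

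Dunnett's test, which uses the shared control, has a two-sided critical value of 2.349. At SD 0.12 it needs 288 × (2.349 + 0.8416)² ≈ 2,932 per arm, and 3,000 per arm gives Φ(3.227 - 2.349) ≈ 81%.

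**The case against.** The strongest reply is that nothing is underpowered. The stated minima do give 80% for each comparison at two-sided 5%. The statistical methods section states no split of alpha, and any multiplicity procedure may sit in an analysis plan that is not shown. The minima are also not the sample: the trial recruits 3,000 per arm per country.

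Most of this stands. A reader might infer, without any condition, that the stated n fails to give 80% power. The documents do not support that, because the shortfall arises only if alpha is split. A reader might also infer that 12,000 per country is too few. That is not supported either: the protocol justifies 12,000 only as giving greater accuracy, power at SD 0.10 is 93%, and the gap at SD 0.12 is 16 per arm (3,016 against 3,000) under Bonferroni and disappears under Dunnett.

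Counting all six pairs would lower power at 3,000 per arm to 89% at SD 0.10 and 72% at SD 0.12. But that puts the video-video contrasts, which the protocol calls exploratory, into one confirmatory family with the primary ones. Even then the pooled power is at least 97%.

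The reply does not rescue the label. Tau could be a true count of two only if there were two one-sided comparisons, and the protocol describes neither. The absence of a multiplicity rule from the analysis section is not the complaint. The complaint is that the sample-size section announces an allowance that its figures do not contain.

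**Conclusion.** The point holds as an error in the sample-size derivation, of moderate weight. Tau is misdefined, the minima of 1,570 and 2,260 contain no multiplicity allowance, and the mention of three groups conflicts with the four-arm design. If the comparison count is honoured for the three video-control contrasts, the minima rise by about a third under two-sided Bonferroni (2,094 / 1,570 = 1.33) or about an eighth under the printed formula (1,764 / 1,570 = 1.12).

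The planned sample is essentially adequate for those three contrasts. What is lost is spare margin in the country-specific analyses at SD 0.12, where power is about 80% before any exclusions, and the protocol drops incomplete responses from analysis. If 5% to 10% were excluded (an assumption, since the protocol gives no rate), Bonferroni power would be about 77% to 75%.

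These figures rest on the protocol's own difference and SDs, on two-sided testing, and on Bonferroni or Dunnett as the adjustment. The protocol fixes neither the sidedness nor the method.

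**What to change.** In the Sample size section:

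1. Write the quantile as Z at 1 - alpha/(2 × tau), so that sidedness and comparison count are separate terms.
2. Set tau = 3, name the three video-control contrasts, and say that the video-video contrasts are exploratory, in line with the section on comparators.
3. Replace the reference to three groups with four arms.
4. Restate the minima as 2,094 per arm (N = 8,376) at SD 0.10 and 3,016 per arm (N = 12,064) at SD 0.12. If Dunnett's test is the intended method, say so and give its figure at SD 0.12 (about 2,932 per arm).
5. State the power of the planned 3,000 per arm per country for these contrasts: 93% at SD 0.10 and about 80% at SD 0.12 (79.8% Bonferroni, about 81% Dunnett), before exclusions, and over 98% pooled.

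The cost is one rewritten paragraph and a less favourable stated minimum: at SD 0.12 the Bonferroni total of 12,064 slightly exceeds the 12,000 per country. No added recruitment is needed. As the Trial status section expects data collection to end by February 2022, this is a correction to the stated justification and leaves the design unchanged.

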## Background and rationale

In the midst of the COVID-19 pandemic, research highlights the critical role of interventions to increase vaccine confidence, even before vaccines for COVID-19 become universally available [1, 2]. The WHO has dubbed vaccine hesitancy one of the greatest threats to global health [3], yet we are lacking interventions that effectively promote vaccine confidence in ways that are accessible and globally scalable. Many existing interventions have focused on providing information in the form of scientific data, using a didactic approach. This strategy has proven ineffective for key target audiences [4].

Designing effective interventions for a broad range of target audiences has become even more important during the COVID-19 pandemic as misinformation has spread rapidly around the world. Negative claims about vaccines often appeal to the emotions of the target audiences, eliciting vaccine doubt and hesitancy. This observation—that emotion-focused messages resonate and affect health behaviors [4, 5]—can also potentially be used to the advantage of health communicators. Research suggests that activating positive emotions, like hope and altruism, can actually bolster vaccine education interventions [5].

Other promising pedagogical strategies, including the use of instructional humor [6], analogies [7, 8], and storytelling, could also be leveraged to promote vaccine confidence, and researchers have advocated for a transdisciplinary approach to successful health communication on vaccines [4]. By integrating different fields of expertise, including those outside of academia—like entertainment and marketing—we may be able to design more effective vaccine promotion interventions. Animated E-E videos, developed using transdisciplinary approaches, could be an especially effective method for distributing evidence-based health messages globally through social media platforms [9, 10].

To improve vaccine confidence, we designed three videos, employing three research-informed pedagogical strategies: (i) a storytelling-instructional-humor approach (ii) a storytelling-analogy approach (iii) a storytelling-emotion-focused approach.

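### The sample size rests on an unsourced SD of 0.10 to 0.12 that is not credible for a 1–5 hesitancy score, so the claim of 80% power for a 0.01-point difference is unsupported

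*Protocol article*

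**What the plan says.** The primary outcome is a hesitancy score, general (nine questions) and COVID-19-specific (seven questions). Under Primary outcome measures, "we will normalize the final score to a range of 1–5 for both measures for comparison", with higher values meaning more hesitancy. Under Statistical methods, Primary outcomes, the score is calculated for each participant, so the SD that matters for power is the between-participant SD.

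In the Sample size section, "we assume that the means of two arms are 2.00 and 2.01", and the SD and the target difference are given together: "the standard deviations are the same, 0.10. To detect a difference of 0.01 between the vaccine hesitancy between arms". On that scale 1 is total acceptance and 5 is complete refusal. With α = 0.05, β = 0.2 and a divisor τ = 2, the section arrives at 1,570 per arm. For sensitivity the authors "change our assumption and increase the standard deviation to 0.12", which gives 2,260 per arm. They then plan 12,000 per country, for greater accuracy. No pilot, publication or argument is given for either SD, and no power is stated for the planned size.

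**The concern.** Mean 2.00 and SD 0.10 describe a population packed tightly around one value on a four-point-wide scale. Almost nobody would be neutral or negative about vaccines. The sensitivity value of 0.12 stays in the same region, so it does not test the assumption.

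This is the document's only power justification. If the true SD is larger, the 0.01-point target is out of reach at the planned size. A reader could then take a non-significant video comparison as informative about differences near 0.01 when the trial had little power there. The exposure is greatest in the country-specific analyses that the protocol plans alongside the pooled one.

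**Working it through.** **Inputs.** From the Sample size section: difference 0.01, SD 0.10 and 0.12, α = 0.05, power 0.80, τ = 2 (so z = 1.960, numerically an ordinary two-sided 5% test), and 12,000 per country. Four equal arms give 12,000 / 4 = 3,000 per arm per country and 6,000 per arm pooled.

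**1. Reproduce the plan.** n per arm = 2 × (SD / 0.01)² × (1.960 + 0.842)².
- SD 0.10: 1,569.8 (plan: 1,570).
- SD 0.12: 2,260.5 (plan: 2,260).

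On these SDs, 3,000 per arm gives 97% and 90% power.

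**2. What the SD implies.** Cantelli's inequality bounds the share scoring at least 1 point above a mean of 2.00, that is, 3 or more: share ≤ SD² / (SD² + 1).
- SD 0.10: 0.0100 / 1.0100 = 1.0%.
- SD 0.12: 0.0144 / 1.0144 = 1.4%.

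This needs only the plan's mean and SD. It does not depend on how the items are scored.

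**3. Break-even SD.** The difference detectable with 80% power is 2.8016 × SD × √(2/n).
- Per country: 2.8016 × √(2/3000) = 0.0723, so 0.01 needs SD ≤ 0.01 / 0.0723 = 0.138.
- Pooled: 2.8016 × √(2/6000) = 0.0511, so SD ≤ 0.196 (0.1955 before rounding).

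At mean 2.00, these limits allow at most 1.9% and 3.7% of participants at 3 or above.

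**4. The same check in reverse.** If a share p scores 3 or more, then SD ≥ √(p / (1 − p)).
- p = 5%: SD ≥ 0.229, so power for 0.01 is at most 39% per country and 67% pooled.
- p = 10%: SD ≥ 0.333, so power is at most 21% and 38%.

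**5. Power over an assumed range of SDs.** The document gives no empirical SD; 0.3 to 0.8 is an assumption. Power is Φ(d − 1.960) + Φ(−d − 1.960), with d = 0.01 / (SD × √(2/n)).

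| SD | Power for 0.01, per country | Power for 0.01, pooled | Detectable difference, per country | Detectable difference, pooled |
|---|---|---|---|---|
| 0.3 | 25% | 45% | 0.022 | 0.015 |
| 0.5 | 12% | 19% | 0.036 | 0.026 |
| 0.8 | 8% | 11% | 0.058 | 0.041 |

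The detectable differences are in scale points, at 80% power and unadjusted. The pooled columns assume the same SD in both countries.

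**6. With multiplicity, per country.** Bonferroni replaces 1.960 by 2.394 (three video–control comparisons) or 2.638 (all six pairs). √(2/3000) = 0.02582.
- Three: (2.394 + 0.842) × 0.02582 = 0.084 SD.
- Six: (2.638 + 0.842) × 0.02582 = 0.090 SD.

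**The case against.** Several points on the other side stand.

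- The calculation has no arithmetic error. The dispute is about an input.
- A reader might infer that the protocol promises 80% power at 3,000 per arm and fails to deliver it. It does not say so: the 80% belongs to 1,570 and 2,260 per arm, and on the stated SDs the planned size exceeds it.
- The true SD is unknown. The Cantelli bound shows that 0.10 is implausible; it does not show that the SD is several times larger. At SD 0.15, power for 0.01 per country is still 73%.
- It is tempting to argue that 0.10 is smaller than one answer step on one item (1/7 = 0.143 or 1/9 = 0.111). That assumes equally weighted five-category items. The note to Table 1 gives only the end labels of the response scale, so the argument is not used here.
- No passage defines a score of 3 as hesitant, and the Background's statement that "The WHO has dubbed vaccine hesitancy one of the greatest threats to global health" says nothing about score distributions in these panels. The plan is therefore not in formal contradiction with its premise. The judgement is one of credibility.
- The protocol nowhere says that a null result will be read as no effect. That is a risk, not a stated intention.
- In standardised terms the assumptions are differences of 0.01 / 0.10 = 0.10 SD and 0.01 / 0.12 = 0.083 SD, and 3,000 per arm detects 0.072 SD whatever the SD is.

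The objection that pooling helps is fair but insufficient, because the break-even SD rises only to 0.196.

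**Conclusion.** The point holds as an input-assumption error. The 80% power claimed for a 0.01-point difference depends on a between-participant SD that has no source and that leaves at most 1.0% to 1.4% of participants at or above the midpoint.

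The conclusion does not hang on the assumed 0.3 to 0.8 range. At a mean of 2.00, 80% power for 0.01 at the planned size already fails if 5% of participants score 3 or more, per country and pooled. The size of the loss does depend on the SD, so it can be given only as a range.

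A reader might go further and call the trial underpowered. The document does not support that: the planned size detects small standardised differences. What fails is the translation into 0.01 scale points.

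**What to change.** Keep 12,000 per country and rewrite the Sample size paragraph.

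- Replace the 0.01-point claim by the standardised difference detectable with 80% power: 0.072 SD per country and 0.051 SD pooled, unadjusted. With Bonferroni per country, state 0.084 SD for the three video–control comparisons or 0.090 SD for all six pairs, whichever family is claimed.
- Add the scale-point equivalents over a stated range of SDs, as in the table above, and give a source for that range if one exists.
- Say that non-significant comparisons will be interpreted against those values, not against 0.01.

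The cost is rewording, with no extra participants and no change to the analysis. The stated detectable difference becomes less favourable.
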